#### Detailed Description of Sessions

##### Session 1: Introduction and Psychoeducation

The first group session (60-120 minutes) opened with introductions and ice-breaking activities to foster a comfortable atmosphere. The clinician presented the group guidelines to ensure a safe and supportive environment. Psychoeducation on trauma and birth trauma followed, with a specific focus on the postpartum period. The clinician then led a discussion on common trauma responses and their neurobiological basis, introducing the concept of healing from trauma through language and memory systems. Participants were encouraged to share coping strategies for triggers. The session included a reflection on personal definitions of “me” and “my space.” As an optional activity, participants engaged in a writing exercise to begin exploring their birth story.

##### Sessions 2-4: Sharing Birth Stories and Narrative Techniques

These sessions (60-120 minutes each) were dedicated to sharing birth stories, with 1 or 2 participants narrating their birthing experiences per session. Through careful questioning, the clinician helped participants use externalizing language to describe their problems (as separate from their personhood versus inherent in them). The clinician then implemented the “outsider witnesses” technique. This is a structured process wherein group members, acting as an audience to the story shared, are invited to reflect on and respond to a person’s story. This involves highlighting significant aspects that stand out, relating them to their own experiences, and describing how the story has impacted them, thereby potentially revealing alternative narratives or overlooked strengths. It usually involves a four-step process (identifying resonant expressions, recognizing values, making personal connections, and acknowledging impact) that validates the storyteller’s experience, while extracting moments of agency and resilience within their narrative. A key focus is the identification of unique outcomes in participants’ stories. The storyteller is then guided through a retelling of their story, incorporating new perspectives and the identified unique outcomes.

##### Session 5: Reflection and Reauthoring

The fifth session (60-120 minutes) began with completing any remaining story sharing, if needed. Participants were then guided to reflect on how their stories felt after sharing and witnessing others’ experiences. The clinician provided them with an opportunity to rewrite or redraw their birth stories, incorporating new insights. Next, the group collaboratively decided on the content for the final session and chose one or more finishing rituals to symbolize consolidation and the end of treatment.

##### Session 6: Integration and Closure

The final session (60-120 minutes) focused on instilling hope by reflecting on changes observed within oneself and others. The clinician guided a reflection on the evolution of birth stories and any emotional shifts experienced (if participants wrote down their birth story after session 1, this was used to facilitate this comparison). The discussion then turned to future directions, exploring values and sources of social support. Participants could revisit and potentially revise their personal definitions of “me” and “my space.” The chosen finishing ritual was completed, providing a sense of closure to the group experience. If desired, participants were given an opportunity to exchange contact information.

#### Outcomes

The following measures were administered according to the schedule depicted earlier in Table 1.

Treatment acceptability was assessed using the Group Cohesiveness Scale (GCS) [46] and the Client Satisfaction Questionnaire (CSQ-8) [47].

The GCS is a 7-item self-report measure assessing the level of cohesiveness in group therapy settings. The scale has strong psychometric properties and is a brief measure of group cohesiveness that can be used in psychiatric settings [46]. The CSQ-8 is a widely used 8-item scale measuring client satisfaction with mental health services. It is a subscale of the original Client Satisfaction Questionnaire-18, which has robust psychometric properties and, combined with its brevity, is a useful brief measure of client satisfaction [48]. The CSQ-8 has been used successfully in the provision of psychological interventions via telehealth (ie, videoconferencing) for conditions such as depression [49].

Treatment feasibility was assessed using indicators of treatment adherence and retention. Based on Wright et al’s [24] research on a virtual psychotherapy group for postpartum mothers, a rate of 70% was set to determine feasibility with respect to individual participant attendance across all the six sessions of the intervention, as well as overall retention (determined by the completion of all postintervention measures after session 6).

Postpartum depression was assessed using the EPDS [50], a 10-item self-report questionnaire widely used to screen for postpartum depression. It assesses symptoms experienced in the past 7 days, with higher scores indicative of a greater endorsement of depressive symptoms. The EPDS has demonstrated good reliability and validity in postpartum women [51] and has been validated for routine postnatal screening in Australia [52].

Postpartum anxiety was assessed using the Perinatal Anxiety Screening Scale (PASS) [53], a 31-item self-report questionnaire designed to screen for anxiety in both antenatal and postpartum women. Developed and validated for use in Australia [53], PASS provides cutoffs for differentiating between minimal, mid-moderate, and severe anxiety [54]. Its strong psychometric properties have led to its cross-cultural use and translation to other languages.

Posttraumatic stress symptoms were assessed using the City Birth Trauma Scale (City BiTS) [55], a 29-item self-report questionnaire specifically designed to measure postpartum PTSD following childbirth. It assesses symptoms based on the *Diagnostic and Statistical Manual of Mental Disorders, Fifth Edition* (DSM-5) diagnostic criteria for PTSD. The scale has shown good reliability and has been validated for use among Australian postpartum women [56].

### Data Analysis

#### Quantitative Data

All analyses will be based on the intention-to-treat principle. The quantitative data analyses will involve repeated-measures ANOVA entering the main effects for group, time, and group×time interaction, assuming α<.05 to denote a significant effect between the IG and the WCG for continuous study outcomes (City BiTS, EPDS, PASS). Assumption testing will examine normality using the Shapiro-Wilk test and sphericity using the Mauchley test of sphericity. Transformation and Huynh-Feldt correction will be applied, respectively, in the case of violation of these assumptions. The therapy process measures will be analyzed for between-group differences to determine the acceptability of the group intervention. As a feasibility and acceptability study, testing the proof of principle, our analyses will provide an estimate of mean (SD) change data and effect sizes to inform a larger trial in the future. The assessment of acceptability and feasibility postdelivery of the intervention, in both the IG and after the last session of the WCG, will afford the trial more quantitative data to identify aspects of the intervention that were perceived as beneficial and preferred.

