**Results:**

The project was funded in March 2024. Recruitment was completed between July and August 2024. Eleven pretreatment sessions were held in August 2024. Of the 33 expressions of interest (EOIs) received by August 2024, 9 participants were recruited and randomized to the IG (n=4, 44.4%) and the WCG (n=5, 55.6%). The IG completed the six-session program between September and October 2024, with data collection finalized for pre-, mid-, and postintervention timepoints. The WCG began receiving the intervention mid-October 2024, with the final data collection in December 2024. Key feasibility and acceptability metrics include attendance rates, participant retention, and group cohesion scores. Data analysis is ongoing, with manuscript preparation planned for mid-late 2025.

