### Sample Size

The study aimed to recruit 16 participants, which was deemed feasible within the project’s funding budget and timelines and is within the recommended size for group-based teletherapy [41]. As a pilot feasibility and acceptability study, should the study be deemed feasible and acceptable, the study findings may help inform estimates for sample size calculation for a larger trial. Consequently, no formal power calculation was performed for this study.

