### Allocation and Concealment

This pilot trial included an IG (who received the intervention immediately after recruitment) and a WCG (who were allocated to a waitlist during the same observation period as the intervention. Although there were no restrictions on outside care for the WCG, no intervention or support was actively offered to these participants. HM monitored the mental health of participants in the WCG (across the outcome measures administered at various timepoints; see Table 1) and alerted the team to any observed deterioration. A recent pilot feasibility trial conducted in Australia noted that people typically wait 6 months or longer to access mental health services [43]. Once the study with the IG concluded, the WCG received the full intervention, which involved a wait time of 6 weeks, significantly less than the typical waitlist.

A randomization sequence in alternating block sizes of 4 and 6 was generated from an online sequence generator by author PJT. The randomization sequence was revealed to the research assistant (HM) and only after completion of the baseline and eligibility measures. At that time, the research assistant informed participants of the intervention start date based on their allocation to either the IG or the WCG.

**Table 1 table1:** Data collection timeline.

Measure	IG^a^ timepoints					WCG^b^ timepoints			
	T1^c^	T2^d^	T3^e^	T4^f^	T1		T2	T3	T4
City BiTS^g^	X^h^	X	X	—^i^	X		X	X	X
EPDS^j^	X	X	X	—	X		X	X	X
PASS^k^	X	X	X	—	X		X	X	X
GCS^l^	—	—	X	—	—		—	—	X
CSQ-8^m^	—	—	X	—	—		—	—	X

^a^IG: intervention group.

^b^WCG: waitlist control group.

^c^T1: prior to session 1 for the IG.

^d^T2: after session 3 for the IG.

^e^T3: after session 6 for the IG.

^f^T4: after session 6 for the WCG.

^g^City BiTS: City Birth Trauma Scale.

^h^X: applicable.

^i^Not applicable.

^j^EPDS: Edinburgh Postnatal Depression Scale.

^k^PASS: Perinatal Anxiety Screening Scale.

^l^GCS: Group Cohesiveness Scale.

^m^CSQ-8: Client Satisfaction Questionnaire.

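### The planned ANOVA names no term as the treatment effect: the group term averages in baseline and the interaction is an omnibus test, so neither gives the promised effect size

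*Protocol article*

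**What the plan says.** The Quantitative Data section of the protocol article specifies "repeated-measures ANOVA entering the main effects for group, time, and group×time interaction". The significance rule attached to this model is worded as "assuming α<.05 to denote a significant effect between the IG and the WCG for continuous study outcomes (City BiTS, EPDS, PASS"). The section does not say which of the three terms decides, or which timepoints enter. It also promises mean (SD) change and effect sizes for a future larger trial, without a timepoint or a baseline adjustment. On model checking it says "Assumption testing will examine normality using the Shapiro-Wilk test and sphericity using the Mauchley test of sphericity", with transformation if normality fails and a Huynh-Feldt correction if sphericity fails.

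Table 1, under Allocation and Concealment, has the three symptom scales at T1, T2 and T3 in both arms and at T4 in the WCG only. Its footnotes read "T1: prior to session 1 for the IG" and "T2: after session 3 for the IG"; T3 follows the IG's session 6. The WCG starts the intervention after the IG has finished.

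Under Sample Size, "The study aimed to recruit 16 participants" and "no formal power calculation was performed for this study". The abstract reports nine women randomized, 4 to the IG and 5 to the WCG.

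**The concern.** A reader who applies the 5% rule has two candidate terms, and neither is the quantity wanted.

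- **Group main effect.** It is the arm difference averaged over all timepoints in the model. T1 comes before treatment, so its expected difference under randomization is zero and it pulls the average towards zero. The phrase about an effect between the IG and the WCG fits this term at least as naturally as the interaction.
- **Group×time interaction.** It asks whether the two profiles differ in any way over three timepoints. A significant F does not say at which time, in which direction or by how much.

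The useful efficacy product of this pilot is an effect size with its uncertainty, for planning the next trial. If the group main effect were carried forward as that effect size, the next trial would be planned on an understated effect. An unadjusted T3 difference would carry any chance baseline imbalance with it, and with 4 and 5 women that imbalance can be large.

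**Working it through.** The plan states no power, SD, effect size or correlation, so there is no planned figure to reproduce. The allocation shares check: 4/9 = 44.4%, 5/9 = 55.6%.

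**Inputs.** From the documents: n = 4 and 5; target 16 (taken as 8 and 8); common times T1 to T3; α = 0.05 (two-sided assumed for single contrasts). Assumed: unit SD, multivariate normal scores, correlation ρ between times, no expected T1 difference.

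**1. What the group main effect estimates.** It is (d1 + d2 + d3)/3, where d is the expected arm difference at each time.
- Linear growth 0, 0.5, 1: 1.5/3 = 0.50 SD
- Late effect 0, 0, 1: 1/3 = 0.33 SD
- Full by T2, 0, 1, 1: 2/3 = 0.67 SD

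The true T3 effect is 1.0 SD in all three. This is algebra and does not depend on ρ.

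**2. Degrees of freedom.** Interaction: (3−1)(2−1) = 2. Its error: (3−1)(9−2) = 14 at N=9 and 2×14 = 28 at N=16. T3 ANCOVA on T1: 9−3 = 6 error df.

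**3. Chance imbalance at T1.** SD of the arm difference = √(1/4 + 1/5) = √0.45 = 0.67. The probability that it exceeds 0.5 SD in either direction is 2[1 − Φ(0.5/0.67)] ≈ 46%.

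**4. Precision at T3.** Per σ²(1/n1 + 1/n2), the variances are:
- ANCOVA: (1 − ρ²)[1 + 1/(N−4)]
- T3−T1 change contrast: 2(1 − ρ)

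The ratio is [(1+ρ)/2][1 + 1/(N−4)]. At N=9 it is below 1 only if (1+ρ)/2 < 1/1.2, that is ρ < 0.67. At N=16 the limit is 0.85. For large N it is below 1 for every ρ < 1.

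**5. Simulated power**, linear effect 0, 0.5, 1 SD, compound symmetry, 20,000 trials per setting, ρ = 0.3 / 0.5 / 0.7 / 0.8:

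| | N=9 | N=16 |
|---|---|---|
| T3 ANCOVA | 24 / 28 / 38 / 49% | 47 / 55 / 70 / 85% |
| 2-df interaction | 16 / 21 / 32 / 46% | 28 / 38 / 59 / 77% |
| Group main effect | 15 / 13 / 11 / 10% | 25 / 21 / 18 / 17% |

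At N=9 the T3−T1 change contrast has 20 / 26 / 39 / 53%. Mean 95% CI half-widths at N=9, in SD units, are 1.63 / 1.47 / 1.22 / 1.03 for ANCOVA and 1.81 / 1.52 / 1.18 / 0.97 for change.

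**6. Where the order reverses at 4 v 5** (interaction v ANCOVA power):
- 0, 1, 1 SD, ρ = 0.7: 42% v 38–39%
- 0, 2, 2 SD, ρ = 0.5: 79–80% v 76–77%
- 0, 2, 2 SD, ρ = 0.7: 95% v 89%
- linear 1 SD, AR(1) 0.8: 37% v 33% (interaction type I error 5.8% here)

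**7. At the scale of a later trial** (64 v 64, T3 effect 0.5 SD, linear), ANCOVA led in every setting run. At ρ = 0.5 it had 90%, against 71% for the interaction and 80% for the change contrast.

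**The case against.** The case for the plan is that repeated-measures ANOVA is a valid model, that the interaction is the conventional test in a pre/mid/post design, and that the text never designates the group main effect as the treatment effect. A T3−T1 contrast can be drawn from the same model. With pooled error and compound symmetry its power is 29%, 44% and 60% at ρ = 0.5, 0.7 and 0.8, against 28%, 38% and 50% for ANCOVA. Mean change and effect sizes are already promised, and the details could sit in a fuller plan. The article itself calls the sample underpowered and says the aim is not to comment on treatment effects.

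Much of this stands, and it limits the point. Three stronger readings are tempting and should not be drawn.

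- **That adjusted T3 is simply more precise or more powerful here.** Steps 4 and 6 show otherwise for nine women, and the documents give no correlation.
- **That adjustment costs a single degree of freedom.** That is true only against an unadjusted T3 test (7 to 6). Against the planned interaction it is 14 to 6.
- **That the normality check is shown to be nearly powerless.** Detecting an exponential distribution in about 12–13% of samples of 4 and 16% of samples of 5 assumes testing within each arm, which the text does not state. With nine pooled values it is 39%. Nor does the text say that the promised mean change would be on a transformed scale.

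The objection does not remove the main gap. The change contrast is not a named test in the plan either, its pooled version relies on sphericity (type I error 9.6% under AR(1) 0.8), and the 5% rule is still attached to a model in which no term is identified as the effect.

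**Conclusion.** The point holds as one about what is estimated. As written, one candidate term understates the T3 effect (0.50 of 1.0 SD under linear growth, 0.33 to 0.67 across the patterns tried) and the other has no single signed estimate. Neither supplies the effect size promised to a later trial.

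The 2-df count is inferred from Table 1, since the analysis section does not list timepoints. It also takes T3 in the WCG as measured before that arm's own sessions, consistent with the described waitlist. All SDs, effects and correlations are assumptions.

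A gain in power or precision is likely at low to moderate baseline correlation but not guaranteed at this size. With half-widths of roughly 1.0 to 1.6 SD, no method will give a tight estimate from nine women. Importance is modest because efficacy is secondary. The change is still worth making, because the article reports analysis as ongoing and the estimate is meant to inform further research.

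**What to change.** In the Quantitative Data section:

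- For each of City BiTS, EPDS and PASS, name as the effect estimate the IG minus WCG difference at T3 adjusted for the T1 score of the same scale (ANCOVA, or a constrained-baseline mixed model on T1 to T3), with a 95% CI.
- Report T2 in the same way, as secondary.
- Keep the repeated-measures ANOVA as descriptive, and state that the group main effect is not read as the treatment effect.
- Keep this estimate in raw scale points whatever the normality test shows.

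The cost is wording and code; all the data are already scheduled. The statistical cost is 6 error df in place of 14 for the planned interaction at N=9. If a fuller analysis plan already names such a contrast, the article's text only needs to be aligned with it.

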### Hypotheses/Research Question

Our first hypothesis is that a narrative-informed, group-based early intervention for postpartum women who have had a traumatic birth experience will be feasible and acceptable. Our second hypothesis is that the intervention will decrease symptoms of postpartum depression, postpartum anxiety, and/or postpartum post-traumatic stress disorder (PTSD) in women with traumatic birth experiences.

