Two coauthors will serve as CPA analysts (CS and HF), the former of whom is also the intervention facilitator. Both CS and HF are experienced in qualitative data analysis. Each analyst will independently review session transcripts (looking at the two initial sessions together, the two second sessions together, and so on) to identify significant process events and extract meanings with respect to context, key responses, and effects. The analysts will also maintain a reflective journal through this process. Once this step is complete, the analysists will meet in the presence of another coauthor (SC), also experienced in qualitative data analysis and not part of the intervention, who will assist in developing consensus through open dialogue, while ensuring that all perspectives are considered and discussed adequately. The multiauthor discussion and review, alongside considerations in the reflective journal, will support the trustworthiness and rigor of the analysis and ensure the analysis best reflects the data and process elements. With this process, we aim to produce a comprehensive understanding of which narrative intervention elements that effectively support birth trauma recovery in a telehealth group setting and which require modification, directly informing intervention refinement for the future. The embedded mixed methods design will allow details of the processes of change in the intervention to complement qualitative findings around feasibility and effectiveness. Outcome data will also be used to triangulate qualitative findings to further support which elements of change were and were not acceptable or useful for participants.

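### The p<.05 rule for IG versus WCG tests whether this one therapy group changed, not whether the intervention works on average; the distortion is modest at 4 v 5 but undisclosed

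*Protocol article*

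**What the plan says.** Below, arm means IG or WCG, and therapy group means the women who meet together.

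- **Hypothesis.** Under Hypotheses/Research Question: "Our second hypothesis is that the intervention will decrease symptoms of postpartum depression, postpartum anxiety", continuing to posttraumatic stress. The claim concerns the intervention, not one delivery of it.
- **Model.** Under Quantitative Data: "repeated-measures ANOVA entering the main effects for group, time, and group×time interaction", followed by "assuming α<.05 to denote a significant effect between the IG and the WCG for continuous study outcomes". The remedies named for violated assumptions are transformation (normality) and the Huynh-Feldt correction (sphericity). No term or adjustment represents the therapy group.
- **Number of therapy groups.** Under Qualitative Data, the transcripts are read "looking at the two initial sessions together, the two second sessions together, and so on". Two transcripts per session number, across both arms, means one therapy group per arm. The Blinding section says that the chief investigator delivered the treatment.
- **Dependence within the therapy group.** In sessions 2–4, "group members, acting as an audience to the story shared, are invited to reflect on and respond to" each woman's story, and the storyteller then retells it with what they contributed.
- **Comparison arm.** Under Allocation and Concealment, the WCG waits during the comparison period and is not actively offered any intervention or support.
- **Numbers.** The Results part of the abstract reports 4 women randomised to the IG and 5 to the WCG. Sample Size says that "no formal power calculation was performed for this study".
- **Limitations.** Listed are small sample, LOCF, selection, the investigator as therapist, and no long-term follow-up. Non-independence is not listed. Dissemination and Scalability mentions multiple groups, but for statistical power.

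**The concern.** The ANOVA judges the IG–WCG difference against variation between women, as though each IG woman had been treated separately. To T3 the design is partially nested: one cluster of treated women against unclustered waiting women. If this therapy group happened to go unusually well or badly as a group, through its mix of members or its rapport, the whole of that swing appears in the contrast. None of it appears in the error term, because the women shared it.

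A result below .05 would then be read as support for the second hypothesis when it might reflect one group's dynamics. The low power that the article admits is a different matter: it concerns missed effects, whereas this concerns false positives. The listed corrections cannot help, since neither addresses independence.

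**Working it through.** **Inputs.** m = 4 IG women, n = 5 WCG women, three timepoints (T1–T3) and α = .05, all from the protocol article. The ICC ρ of IG women's T1–T3 change is not in the document; 0.05 to 0.30 is assumed.

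**Nominal level first.** With ρ = 0, 200,000 simulated trials at 4 v 5 reject in 5.05% for the group×time F test (2 and 14 df) and 4.94% for the t test on T1–T3 change (7 df). The stated 5% is reproduced when women are independent.

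**Adding one shared IG effect.** The true intervention effect, averaged over therapy groups, is set to zero. The shared effect is absent at T1, half-grown at T2 and full at T3. WCG women stay independent. Two set-ups were used.

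*A. Total variance of change fixed at 1.*
- True SE² = [1+(m−1)ρ]/m + 1/n
- SE² that the model expects = {[(m−1)(1−ρ)+(n−1)]/(m+n−2)} × (1/m+1/n)
- At ρ = 0.20: true = 1.6/4 + 0.2 = 0.600; model = (2.4+4)/7 × 0.45 = 0.411; ratio of SEs = √(0.600/0.411) = 1.21.

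*B. Shared effect added to a between-woman variance of 1, so its variance is ρ/(1−ρ).*
- True SE² = ρ/(1−ρ) + 1/m + 1/n; model SE² = 1/m + 1/n = 0.45
- At ρ = 0.20: true = 0.25 + 0.45 = 0.70; ratio of SEs = √(0.70/0.45) = 1.25.
- The change test then rejects with probability P(|t₇| > 2.365/1.247) = P(|t₇| > 1.90), about 10%.

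**Results at 4 v 5** (range over the two set-ups):

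| Assumed ICC | True SE / model SE | Error rate, group×time | Error rate, T1–T3 change |
|---|---|---|---|
| 0.05 | 1.05–1.06 | 5.6–5.7% | 6.0% |
| 0.10 | 1.10–1.12 | 6.2–6.6% | 6.9–7.2% |
| 0.20 | 1.21–1.25 | 8.0–8.9% | 9.2–10.0% |
| 0.30 | 1.31–1.40 | 9.8–11.7% | 11.6–13.5% |

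**Why the IG–WCG data cannot repair this.** Estimating between-group variance among treated women needs at least two treated groups over the same comparison. There is one, so the component has 1 − 1 = 0 degrees of freedom and is fully confounded with arm.

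**Multiplier for a sensitivity interval.** The variance observed within a single group estimates only (1−ρ) of the total, because the shared part cancels. The observed IG variance of the mean must therefore be multiplied by [1+(m−1)ρ]/(1−ρ). At m = 4:
- ρ = 0.05: 1.15/0.95 = 1.21
- ρ = 0.10: 1.30/0.90 = 1.44
- ρ = 0.20: 1.60/0.80 = 2.00

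The usual design effect alone (1.15, 1.30, 1.60) would be too small.

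**The case against.** The strongest reply has five parts.

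1. **Randomisation protects the test.** Women were individually randomised, so a reader who infers that the test is invalid outright goes too far. It remains a fair test of the null that attending this group changed nothing. Peer response is also part of the treatment, so some shared movement is treatment effect. This stands. What fails is the step from this group to the intervention averaged over groups, which is the step that the second hypothesis takes.
2. **The size is small.** This stands for low ICC: at 0.10 or below, the group×time error rate exceeds 5% by at most about 1.6 percentage points. No figure in the article fixes the ICC, so strong inflation cannot be asserted.
3. **The target of 16 would look worse.** A reader might quote 8 v 8, where group×time rejection at an ICC of 0.20 is roughly 12–13%. That assumes an equal split and does not describe the trial as randomised.
4. **Intervals.** A reader might infer that published confidence intervals will be too narrow. The article announces p values, mean (SD) change and effect sizes, but no intervals. The point applies only if one is built from this model.
5. **It is a pilot, and significance is disclaimed.** The limitations say that commenting on significant effects is not the aim, and they disclose the investigator as therapist. This lowers the stakes. It does not remove the rule under Quantitative Data or supply the missing caveat, and it makes dropping the rule easy.

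**Conclusion.** The point holds in a limited form. The planned p value for IG versus WCG is not a valid test of the second hypothesis, because one therapy group under one clinician stands for the intervention and the model has no such level. The article does not say so. The direction of the error, too many rejections, requires a positive ICC. Its size rests on an assumed ICC and on a shared effect that builds steadily to T3: at 4 v 5 it is slight at 0.05, modest at 0.10, and approaches twice the nominal rate only at about 0.20 to 0.30. The feasibility and acceptability criteria are unaffected.

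**What to change.** - **Quantitative Data.** Remove the α<.05 rule as the reading of the IG–WCG contrast. Report T1–T3 mean (SD) change and effect sizes by arm descriptively, which agrees with the aim stated in the limitations.
- **Same section.** State that the contrast cannot separate the intervention from this one therapy group and clinician. Show the WCG's own T3–T4 change beside it, as a second treated group. Two groups cannot usefully estimate between-group variance, but the comparison gives a descriptive check on whether a swing was peculiar to one of them.
- **Study Limitations.** Add one sentence on non-independence of women within the therapy group.
- **If an interval is reported.** Add a sensitivity table that multiplies the observed IG variance of the mean by [1+(m−1)×ICC]/(1−ICC), with m the number of IG women analysed and ICC 0.05, 0.10 and 0.20. Apply no inflation to the WCG, which is ungrouped up to T3.

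The cost is a few sentences and possibly one small table, with no new data. The downside is wider intervals and no significance claim for the symptom outcomes.
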